### Safety Assessment

All adverse events (AEs) will be recorded during the trial and ranked as mild (does not affect the normal function of the patient), moderate (affects normal function to a certain extent), or severe (significantly affects normal function). Acupuncture syncope, pain at the acupuncture point, bleeding, hematoma, or infection that may occur during acupuncture; patients developing symptoms that are significantly unrelated to the current disease, including an exacerbation of a preexisting disease; abnormalities in medical detection or physical examination that require clinical treatment or further examination; and injury or accident are considered as AEs.

Any medical conditions (eg, vertigo) and accidents should be reported as 2 different AEs. Abnormalities found by laboratory tests, when related to another reported event or that require clinical treatment or further investigation, should be described in the remark’s column of the record and not treated as a separate AE.

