### Control Group

The 8-week CBT-I intervention consists of 1 face-to-face session weekly for a total of 8 sessions with a certified psychologist. Each session will be 45 minutes at a fixed time including setting objectives, learning skills, class activities, and assigning homework. The CBT-I protocol covers typical CBT-I components. The first face-to-face session will include an introduction by the therapist and CBT. After assessing the patient’s condition, the therapist will introduce the insomnia psychological patterns to stimulate the patient’s intention for the therapy. In the second session, the therapist will set sleep restriction and stimulation control strategies based on the first conversation and carry out targeted sleep education. Starting with the third session, the therapist will map the patient’s sleep diary and assess compliance to determine whether uptitration is allowed. Cognitive therapy for negative sleep beliefs will be performed from session 5. The principles of confidentiality, adherence, and autonomy will be followed throughout. At the end of each session, the therapist will assign homework to the participant and summarize the content of each treatment to provide skill consolidation and relapse prevention.

We will ensure patient confidentiality during the interview process and only mention the questions in treatment; no one shall disclose relevant information except the medical staff responsible for treatment. The client is expected to actively participate in the treatment process and, although there may be unforeseen events, we trust that the participant will adhere to the complete treatment process. Participants may leave the trial at any time during treatment. If, for some reason, the participant does choose to leave, there will be no effect on future treatment.

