### Statistical Analysis

If statistical demographic data and other baseline characteristics are continuous variables, they will be represented by the mean (SDs) and median (IQR) values. We will also include count and grade data for frequency and composition ratios. Concomitant medications will be categorized using the Anatomical Therapeutic Chemical code, percentage of patients with concomitant medications, and the incidence of AEs will be compared using the *χ*^2^ test or Fisher precision probability.

After 8 weeks of intervention, the change in the ISI score will be compared with the baseline. The subgroups and baseline are used as covariates to compare the differences between groups by analysis of covariance and the 2-sided 95% CIs of the least squares mean differences between groups. During each visit, the ISI score will be recorded, and mixed-effects model repeated measures will be used to compare the differences between groups. To compare 2 independent samples, a 2-tailed *t* test or nonparametric test will be used for continuous data, and chi-square or Fisher exact or nonparametric tests will be used for categorical data. The times and number of drugs that are taken by participants will be compared between groups using a rank sum test. When a covariance analysis is used for the primary efficacy indicator, missing values will be filled using the last observation carried forward method. When using the mixed-effects model repeated measures method for analysis, the missing data will not be filled. When an outlier is found, the main researcher, the applicant, and the statistician will discuss the processing method together before the database is locked. If necessary, the outlier value will be removed for sensitivity analysis.

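### The adverse event rules classify a stand-alone laboratory abnormality two ways and, by implication, may leave worsening of insomnia or menopausal symptoms uncounted, which could under-count events in CBT-I relative to EA

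*Protocol article*

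**What the plan says.** The AE rules are in the protocol article, Methods, Safety Assessment. The section opens by saying that all AEs are recorded and graded in three severity levels. It then lists what is considered an AE:

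- Procedure events: "Acupuncture syncope, pain at the acupuncture point, bleeding, hematoma, or infection that may occur during acupuncture".
- Symptoms: "patients developing symptoms that are significantly unrelated to the current disease, including an exacerbation of a preexisting disease".
- Findings on testing: "abnormalities in medical detection or physical examination that require clinical treatment or further examination".
- Injury or accident.

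The second paragraph adds a rule for laboratory results. Its scope is "Abnormalities found by laboratory tests, when related to another reported event or that require clinical treatment or further investigation". The instruction given for every result within that scope is that it "should be described in the remark’s column of the record and not treated as a separate AE".

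Three other places bear on the point. The abstract's Objective makes comparison of safety an aim alongside effectiveness. Statistical Analysis states that "the incidence of AEs will be compared using" a chi-square or Fisher test. Under Control Group, at the second CBT-I session, "the therapist will set sleep restriction and stimulation control strategies". Table 1 has one AE row for both arms, ticked at weeks 4, 8, 12 and 20.

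**The concern.** There are two separate problems.

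The first is a contradiction. The laboratory rule has two triggers joined by *or*: a link to another reported event, or a need for treatment or investigation. With the first trigger alone it would be an ordinary rule against double counting. The second trigger takes out findings that the preceding paragraph puts in. Two people coding the same result could each follow the text and disagree.

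The second is a gap. The one symptom category is limited to symptoms unrelated to the disease under study. CBT-I is a treatment that acts on sleep itself, so a plausible harm of it would resemble the disease. The plausible harms of EA are needle events, and these are named individually. If site staff take the list as complete, the count is more likely to reach EA's harms than CBT-I's.

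At stake is the between-arm comparison of AE incidence. The primary noninferiority conclusion on the ISI is not at stake.

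**Working it through.** No figure in the plan can be reproduced here, because the article gives no AE rates. The main check is to set the rules side by side.

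**1. How each kind of event is classified**

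| Event | Paragraph 1 | Paragraph 2 | Result |
|---|---|---|---|
| Laboratory abnormality that is part of another reported event | AE if it needs action | Remark | Remark; reasonable, avoids double counting |
| Laboratory abnormality, no parent event, needs treatment or work-up | AE | Remark, not a separate AE | Contradiction |
| Needle event | AE, named | – | Counted |
| New symptom unrelated to the disease | AE | – | Counted |
| Worsening insomnia or menopausal symptoms | Not listed | – | Unclear |

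The last row is not settled by the words "patients developing symptoms that are significantly unrelated to the current disease, including an exacerbation of a preexisting disease". Insomnia of more than 3 months is an inclusion criterion, so its worsening is arguably an exacerbation of a preexisting disease. It is equally a symptom related to the current disease, which the same phrase leaves out.

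**2. Which problem can differ between arms**

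The laboratory rule is the same for both arms, and the only laboratory test in Table 1 is serum sex hormones at baseline and week 8. By itself it does not favour either arm.

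The symptom wording is also the same for both arms. It distorts the comparison only if disease-like worsening is more frequent in one arm. Sleep restriction makes that plausible for CBT-I, but the documents do not show it.

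**3. Sensitivity of the planned test (assumed counts, for illustration only)**

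Inputs: 160 randomized 1:1, so 160/2 = 80 per arm (from the article). The counts of patients with an AE are assumptions. Test: two-sided Fisher exact.

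For 8 EA patients against 0 in CBT-I, the probability that all 8 fall in EA is C(80,8)/C(160,8) = 0.00325. Doubling it by symmetry gives p = 0.0065.

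Symptom gap, varying the CBT-I patients whose disease-related events are counted:

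| EA patients with needle events | CBT-I 0 | CBT-I 4 | CBT-I 8 |
|---|---|---|---|
| 8 | p = 0.0065 | p = 0.37 | p = 1.00 |
| 16 | p = 0.00001 | p = 0.007 | p = 0.12 |

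In the first row the risk difference goes from 8/80 − 0/80 = 10 points, to 8/80 − 4/80 = 5 points, to 0.

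Laboratory rule, starting from 8 against 0 and adding the same number of patients with only a laboratory AE to each arm:

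| Added per arm | EA vs CBT-I | p |
|---|---|---|
| 0 | 8 vs 0 | 0.0065 |
| 2 | 10 vs 2 | 0.032 |
| 4 | 12 vs 4 | 0.062 |
| 8 | 16 vs 8 | 0.12 |

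Here the risk difference stays at 8/80 = 10 points throughout and only the p value moves.

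A handful of reclassified patients per arm can change the test result. The tables say nothing about how many to expect.

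**The case against.** The strongest reply has four parts.

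- **The laboratory sentence is a wording slip with little to act on.** It follows a counting rule and speaks of a separate AE, so its purpose is probably to stop double counting. No safety laboratory panel appears in the schedule. The point about scale stands. The contradiction remains, because the text as printed gives the opposite instruction. Reading the medical detection item in paragraph 1 as non-laboratory tests would remove the conflict, but nothing in the article says so.
- **The article never says that disease worsening is not an AE.** It says all AEs are recorded, and the list contains no word such as *only*. This stands: the exclusion is by implication. But the list follows directly as the statement of what is considered an AE, so the general sentence does not settle the matter.
- **Worsening is measured anyway.** ISI and Menopause-Specific Quality of Life are collected at weeks 4, 8, 12 and 20, and the other scales at week 8. The information is therefore not lost. Group mean changes, however, do not count patients harmed, and they do not enter the AE incidence.
- **Any under-count in CBT-I works against EA.** This is correct: the error would not flatter the experimental treatment. It would still misstate the safety comparison.

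A reader might infer more: that the AE comparison as a whole is undefined, or that the laboratory rule is itself lopsided. The documents support neither. Needle events, unrelated symptoms, examination findings and injuries are all defined, the test is named, and the laboratory rule treats both arms alike. Nor do the documents give a basis for any particular number of uncounted CBT-I patients.

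**Conclusion.** The concern holds in a limited form. One class of event, the stand-alone laboratory abnormality that needs action, is classified in two incompatible ways. This is a plain contradiction in the text, equal in both arms, and probably small given what is scheduled.

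Separately, worsening of insomnia or menopausal symptoms is absent from the listed categories, while five acupuncture events and no CBT-I events are named. AE incidence could therefore be under-counted in CBT-I relative to EA, making EA look worse. That rests on two assumptions: that staff treat the list as complete, and that CBT-I produces more disease-like worsening than EA. The documents establish neither and give no rates, so the size is unknown.

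The point is worth correcting because safety is a stated objective, AE incidence is tested between arms, and the correction is cheap.

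**What to change.** Make two wording changes in Safety Assessment, carried into the eCRF instructions.

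1. Laboratory findings: an abnormality goes in the remarks column only when it is part of an AE already reported. An abnormality that stands alone and needs treatment or investigation is an AE.
2. One AE definition for both arms, which expressly includes worsening of insomnia or menopausal symptoms. Relation to treatment and to the underlying condition is recorded as a separate item and does not decide whether the event is entered. The needle events can stay as examples.

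No new visits are needed: the AE row of Table 1 already covers weeks 4, 8, 12 and 20 in both arms.

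The cost is revised protocol and eCRF wording and slightly more AE entries. Recruitment began in January 2023, so the date of the change should be recorded, and events entered earlier should be checked against the revised rule where source records allow. The primary ISI analysis does not change.

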### Statistical Analysis

If statistical demographic data and other baseline characteristics are continuous variables, they will be represented by the mean (SDs) and median (IQR) values. We will also include count and grade data for frequency and composition ratios. Concomitant medications will be categorized using the Anatomical Therapeutic Chemical code, percentage of patients with concomitant medications, and the incidence of AEs will be compared using the *χ*^2^ test or Fisher precision probability.

After 8 weeks of intervention, the change in the ISI score will be compared with the baseline. The subgroups and baseline are used as covariates to compare the differences between groups by analysis of covariance and the 2-sided 95% CIs of the least squares mean differences between groups. During each visit, the ISI score will be recorded, and mixed-effects model repeated measures will be used to compare the differences between groups. To compare 2 independent samples, a 2-tailed *t* test or nonparametric test will be used for continuous data, and chi-square or Fisher exact or nonparametric tests will be used for categorical data. The times and number of drugs that are taken by participants will be compared between groups using a rank sum test. When a covariance analysis is used for the primary efficacy indicator, missing values will be filled using the last observation carried forward method. When using the mixed-effects model repeated measures method for analysis, the missing data will not be filled. When an outlier is found, the main researcher, the applicant, and the statistician will discuss the processing method together before the database is locked. If necessary, the outlier value will be removed for sensitivity analysis.

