### Participants

The sample size is based on the ISI. After 8 weeks of intervention, the mean ISI score baseline changes are approximately –7.7 (4.18) [21,32]. Assuming that the ISI score of the acupuncture group is slightly lower than that of the CBT group after 8 weeks of treatment, the ISI score should be no more than –2, with a noninferior effect threshold of –4 [33]—assuming that the single-side significant level is α=.025, power of the trial is 1 – β=.80, and the ratio between the EA group and the CBT-I group is 1:1. As calculated by PASS software (IBM Corp), each group requires 71 cases. Assuming that the dropout rate is 10%, the final sample size should be 160.

Eligible patients will be randomly assigned to either the EA or CBT-I group and will receive EA treatment or CBT-I consultation, respectively. The inclusion criteria are the International Classification of Sleep Disorders (Third Edition) criteria for insomnia disorder; women aged 40-60 years; according to STRAW+10 (Stages of Reproductive Aging Workshop + 10), signs of menopausal tendency that began to appear from clinical features, endocrinology, and biology until 1 year after final menopause; insomnia lasting for >3 months; total ISI score >14; and willingness to participate in the investigation and provide written informed consent prior to the trial.

The exclusion criteria are the use of menopause hormone therapy and sedative or antianxiety drugs; nonnatural menopause (due to surgery, radiation, and medication); any diseases that cause sleep disturbance; unknown causes of vaginal hemorrhage; diagnosis of mental disorders or any serious physical illness; receipt of CBT or acupuncture for insomnia; participation in any other clinical trial within the last 6 months; and pregnancy or lactation.

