### Randomization and Blinding

This study uses a randomized block design. Individual random numbers will be generated with SAS (version 9.4; SAS Institute). The random table is reproducible, and the random seeds will be recorded in the file. A researcher who will not interact with the participants during the recruitment or interventions will take charge of using sealed opaque envelopes to keep the randomized allocation sequence. The trial is designed to be open-ended, but the evaluators will be blinded to patient group assignments. The therapists who administer the treatment are not involved in the evaluation of the trial.

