### Treatment

Treatment group participants will receive acupuncture treatment from the same acupuncturist. The temperature of the treatment room will not be lower than 25 °C. Patients in the EA group will be treated with 0.25×25 mm and 0.25×40 mm disposable steel needles (Guizhou Andi Medical Instrument Co, Ltd).

Patients will be positioned supine after local skin disinfection with 75% alcohol wipes. The acupuncturist will insert needles into the GV20 (Baihui), DU24 (Shenting), EX-HN3 (Yintang), EX-HN18 (Anmian), EX-CA1 (Zigong), RN6 (Qihai), and RN4 (Guanyuan) acupoints as per the WHO Standard Acupuncture Point Locations [34]. KI3 (Taixi), KI7 (Fuliu), HT7 (Shenmen), and SP6 (Sanyinjiao) may also be used accordingly. KI3 and KI7 may be used for hot flashes; HT7 and SP6 are used for anxiety and depression. The needle is inserted with the double hand-needle insertion technique at a depth adjusted based on the standard permissible depth of insertion for each acupoint. The needle is then twirled, rotated, lifted, and thrust moderately until achieving the *deqi* sensation.

An electric stimulator will be placed on the pair of GV20 and EX-HN3 points with a continuous wave, 2.5 Hz, and 4-5 mA, for 30 minutes in each session. The other needles are retained for 30 minutes and manipulated for 10 seconds, twice every 10 minutes, with intermittent stimulation.

The needles will be removed with clean cotton balls to avoid bleeding. Each patient will receive 20 sessions over 8 weeks as follows: 3 per week in the first 4 weeks, every 2 days, with a 1-day interval; and 2 per week in the following 4 weeks, every 3 days, with a 2-day interval.

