### Outcome Measures

The primary outcome will be a mean change in total ISI from baseline to the end of the 8-week intervention. The validated ISI that has a concise design, good reliability, and has become a recognized tool for clinical researchers to evaluate the efficacy of insomnia will be used [35,36]. The ISI is a self-reporting questionnaire, and 7 self-rated items are included that evaluate the severity and impact of insomnia on patients. The total ISI score ranges from 0 to 28 points. The higher the score, the more serious the degree of insomnia, which is classified according to the total score (0-7 points represent clinically nonsignificant insomnia, 8-14 points represent subthreshold insomnia, 15-21 points represent moderately severe clinical insomnia, and 22-28 points represent severe clinical insomnia).

The secondary outcomes include the Menopause-Specific Quality of Life (MENQOL); Menopause Rating Scale; PSQI; Hamilton Depression Scale (HAMD); Hamilton Anxiety Scale (HAMA); hot flash score; and the level of estradiol, follicle-stimulating hormone, and luteinizing hormone in serum. Sleep architecture will be assessed using deep learning on polysomnograms (PSG). The ISI and MENQOL are measured at randomization and 4, 8, 12, and 20 weeks after randomization. The other outcomes are measured before and 8 weeks after randomization.

Menopause Rating Scale is a reliable method to measure the severity of menopausal compliance and contains 11 items in 3 dimensions (psychological, somatic-vegetative, and genitourinary systems). Each symptom is given a score of 0, 1, 2, 3, and 4 according to severity; the total is the sum of the scores of each item [37,38].

The PSQI scale is used to assess the quality of sleep during the previous month [39]. The scale consists of 9 questions, and the overall score ranges from 0 to 21. The higher the score, the worse the sleep quality. PSQI can be used to calculate patient sleep onset latency, time in bed, wake after sleep onset, total sleep time, sleep efficiency, and record the medicine used. Therefore, the combination of sleep quality and quantity can be used to assess sleep conditions and identify any sleep disorders.

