The HAMD was developed by Hamilton [40] in 1960 to test the severity of depression in participants. The scale evaluation method is simple and is most used in clinical practice. The time frame for the assessment is the last 1 week. Two trained assessors jointly examine and score the patient by means of a conversation. A version with 17 items will be used in this study with scores of 0-7 regarded as having no depressive symptoms, 8-17 regarded as having mild depression, 18-24 regarded as having moderate depression, and 25-52 regarded as having major depression.

The HAMA scale uses conversation, observation, and independent grading to rate anxiety in the previous week. There are 14 items, and anxiety is scored as 0 to 4 (0: none; 1: mild; 2: moderate; 3: severe, and 4: very severe). The total ranges from 0 to 56 points, and the higher the score, the more severe the anxiety symptoms [41]. HAMA can also be used to assess medication use and the effect of psychological intervention.

Participants will complete validated hot-flash daily diaries for 7 days at baseline and 8 weeks after randomization, by recording the number of hot flashes and severity (mild, moderate, severe, or very severe). A composite score is generated by multiplying the number of mild, moderate, severe, or very severe hot flashes by 1, 2, 3, and 4, respectively, and summing the values into one score [42].

MENQOL is used to record the symptoms experienced by participants in the past month or to evaluate the clinical efficacy of quality of life in menopausal women. MENQOL includes 29 items, each with a score of 0-6; 0 means the symptom has no impact, and 6 means extreme impact. The scale records symptoms in the 4 domains such as vasomotor, somatic symptoms, psychological symptoms, and sexuality. The higher the score, the worse the patient’s quality of life [43].

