Women who are undergoing menopause transition seem to report more sleep difficulties. The content of some hormone changes dramatically in this stage, which may be associated with decreased melatonin synthesis and secretion. Progesterone reduces arousal and can have a sedative effect, while estrogen increases the turnover of the neurotransmitter norepinephrine and, subsequently, increases time spent in REM sleep and decreases REM latency [54]. Many of the menopausal symptoms (eg, hot flashes and night sweating) are precipitating factors for insomnia, which are in relation to the occurrence of poor sleep quality in menopausal women. Hot flashes are one of the most typical menopausal symptoms and are highly associated with awakening perimenopausal women in particular [55]. Repeated exposure to menopausal symptoms that cause wakefulness at night may perpetuate insomnia symptoms through conditioned arousal.

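### The primary ANCOVA is valid and adequately powered, but it leaves unused the baseline hot flash score and HAMA, which could be prespecified as covariates for a modest gain in precision

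*Protocol article*

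**What the plan says.** **Primary analysis.** The endpoint, in Outcome Measures, is: "The primary outcome will be a mean change in total ISI from baseline to the end of the 8-week intervention". Statistical Analysis gives the model: "The subgroups and baseline are used as covariates to compare the differences between groups by analysis of covariance". The group difference is reported with a two-sided 95% CI. The word *subgroups* is not defined, and *baseline* is not spelled out as baseline ISI. No other covariate is named. A mixed model for repeated measures is also planned, with no covariates stated for it.

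**Randomization.** "This study uses a randomized block design". No stratification factor is named.

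**Hot flashes and mood.** The Discussion (Principal Findings) counts hot flashes among the symptoms that set off insomnia and says: "Hot flashes are one of the most typical menopausal symptoms and are highly associated with awakening perimenopausal women in particular". Outcome Measures adds: "Participants will complete validated hot-flash daily diaries for 7 days at baseline and 8 weeks after randomization". Table 1 schedules the hot flash measure and HAMA at baseline and week 8, and Outcome Measures places the first of these before randomization. The Treatment section allows optional acupoints by symptom: "KI3 and KI7 may be used for hot flashes; HT7 and SP6 are used for anxiety and depression".

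**The concern.** A baseline variable that predicts the outcome can be added to an ANCOVA to remove variance from the treatment comparison. By the protocol's own account, hot flash burden is a candidate. It is recorded for every participant before randomization, nothing described in the randomization balances it, and the entry criteria set no limit on it. HAMA is recorded on the same schedule.

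The noninferiority conclusion depends on the width of one confidence interval. The Participants section appears to assume a 2-point deficit for EA against a 4-point margin, which leaves 2 points of room. Variance that a prespecified covariate could have removed uses up part of that room. The adjustment is credible only if fixed before unblinding; added later, it would look chosen by result.

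**Working it through.** **Inputs from the protocol (Participants section).** SD of ISI change 4.18; assumed deficit 2; margin 4; "the single-side significant level is α=.025"; "power of the trial is 1 – β=.80"; 1:1 allocation; 71 per group; 10% dropout; 160 in total.

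**Input not in the protocol.** The share of the variance of ISI change explained by hot flash score and HAMA beyond baseline ISI (R²). I assume 0.02 to 0.10.

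**Step 1: reproduce the stated sample size.** n per group = 2 × 4.18² × (1.96 + 0.8416)² / (4 − 2)² = 68.6, so 69. With the noncentral t distribution it is 70. The stated 71 agrees to within two. Dropout: 142 / 0.9 = 157.8, so 158, against the stated 160. The calculation uses the SD of raw change and relies on no covariate gain.

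**Step 2: precision and power without the extra covariates.** With 71 analysed per group, SE = 4.18 × √(2/71) = 0.702. Power = Φ(2/0.702 − 1.96) = 0.813. The CI half-width is 1.96 × 0.702 = 1.375 ISI points.

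**Step 3: add the covariates.** SE becomes 0.702 × √(1 − R²).

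| Assumed added R² | Power at 71 per group | CI half-width | CI width relative to none | n per group for 80% power |
|---|---|---|---|---|
| 0 | 0.813 | 1.375 | 1.000 | 69 |
| 0.02 | 0.821 | 1.361 | 0.990 | 68 |
| 0.05 | 0.833 | 1.340 | 0.975 | 66 |
| 0.10 | 0.852 | 1.304 | 0.949 | 62 |

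With the t distribution and two degrees of freedom removed, power is 0.816, 0.828 and 0.847 for the last three rows, against 0.808 with no added R². The lost degrees of freedom do not matter.

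**Step 4: chance imbalance.** Imbalance in the covariates moves the unadjusted difference with an SD of 0.702 × √R². That is 0.157 points at R² = 0.05 (95% range ±0.31) and 0.222 at R² = 0.10 (±0.44). These are not additional to Step 3. At R² = 0.05 the adjusted variance is 0.492 × 0.95 = 0.468 and the imbalance variance is 0.157² = 0.025; together they give 0.492 (rounded), the variance in Step 2. The unadjusted CI already covers the imbalance.

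**Step 5: the starting point.** Step 3 begins from the SE of raw change, while the planned model already adjusts for baseline. If baseline ISI explained, say, 10% of the variance of change, power would start at 0.852. A further 5% of the total variance would then take it to 0.871. The increment is 1.9 points, against 2.0 points (0.813 to 0.833) from the raw start. The increments in the table are therefore slightly high, and the starting power slightly low.

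**The case against.** The strongest reply is that nothing here is wrong. A baseline-adjusted ANCOVA in a randomized trial is valid, the sample size was set without any covariate gain, and its power target is met. All of this stands.

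It can also be said that a covariate list belongs in an analysis plan that is not shown. That stands only in part. The article does name a covariate set, so this is a suggested change to a stated model, not a complaint about missing detail.

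A reader might go further and infer several things that the documents do not support:

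- **That the model certainly contains baseline ISI and nothing else.** This is the likeliest reading, but *subgroups* is undefined and could mean other factors.
- **That planned power is lost, or that the estimate is biased.** Neither follows; see Steps 1 and 2.
- **That imbalance and imprecision are two separate harms.** They are one variance component (Step 4), and only half of such imbalances would disfavour EA.
- **That the covariates are known to be strong predictors.** The Discussion links hot flashes to waking and says that they may perpetuate insomnia. It does not say that they predict 8-week change once baseline ISI is known.

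The case for HAMA is thinner than for hot flashes. The Discussion's account of what triggers insomnia does not name anxiety, and excluding diagnosed mental disorders and antianxiety drugs probably narrows its range. The choice of acupoints by symptom describes how EA is delivered; it is not evidence of prognosis in both arms.

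Lastly, the change is not entirely free: a 7-day diary can be incomplete, and a covariate in the primary model needs a value for everyone.

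**Conclusion.** The point holds as an optional efficiency gain, not as an error. The planned analysis is valid and meets its stated 80% power. Prespecifying baseline hot flash score and HAMA would raise power from about 81% to about 82–85% and narrow the CI by about 1–5%. These figures assume an added R² of 0.02 to 0.10, 71 women analysed per group, an SD of 4.18 and a true deficit of 2 points. The R² range is mine; the document offers nothing to narrow it. Hot flash score has a documentary basis as a covariate, whereas HAMA rests more on general plausibility.

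**What to change.** Before unblinding, replace the covariate sentence with an explicit model:

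- **Primary ANCOVA:** ISI change at week 8 on treatment group, baseline ISI and baseline hot flash score (for example as log(1 + score), since such scores are often skewed), with baseline HAMA as a further prespecified covariate. This wording also settles what *subgroups* and *baseline* mean.
- **Mixed model:** the same baseline covariates.
- **Missing baseline covariates:** simple imputation that ignores treatment arm, with the rule for incomplete diaries written down in advance.
- **Sensitivity analysis:** the model with baseline ISI alone.

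The cost is a few sentences, two of about 140 degrees of freedom, and the handling of a few incomplete diaries. No new data and no change to the sample size are needed.
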